# Effect of open versus closed endotracheal suctioning on intracranial pressure in severe brain‐injured children: Study protocol for a randomized controlled trial

**DOI:** 10.1002/nop2.656

**Published:** 2021-05-26

**Keywords:** brain injury, children, intracranial pressure, mechanical ventilation; airway, suction

## Abstract

**Aim:**

To compare the effects and safety of open and closed endotracheal suction in children with severe brain injury.

**Design:**

A single‐blinding, single‐centre randomized controlled trial (RCT).

**Methods:**

The children with severe brain injury admitted to the intensive care unit (ICU) from 1 September 2020–31 August 2022 will be included. And a total of 172 children with severe brain injury are expected to be included. The intracranial pressure, SpO_2_ and heart rate before suctioning, at the end of suction, and at 5 and 10 min after suction, the estimated sputum volume for each suction, the incidence of ventilator‐associated pneumonia, the duration of mechanical ventilation and the length of ICU stay will be analysed.

**Results:**

This present RCT has been prospectively registered in China Clinical Trial Registry (http://www.chictr.org.cn, ChiCTR2000030963). This present study is expected to provide reliable evidence to the airway management in children with severe brain injury.

AbbreviationsICPintracranial pressureICUintensive care unitRCTrandomized controlled trial
*SD*
standard deviationSICUsurgical intensive care unitVAPventilator‐associated pneumonia

## BACKGROUND

1

Brain injury is a common serious problem with extremely high mortality and disability rates in clinical settings, which is very common in car or fall accidents (Capizzi et al., 2020). It has been reported that the incidence of traumatic brain injury ranks the second among the trauma of various body organs, but the mortality of traumatic brain injury ranks the first (Dewan et al., 2016). Previous studies (Cheng et al., 2017; Taylor et al., 2017) have reported that the mortality of patients with moderate‐to‐severe brain injury in the paediatric intensive care unit (ICU) can be up to 41.9%. The brain injury not only poses a serious threat to the life and health of patients, but also places a heavy economic and spiritual burden on their families and society (Steinbuchel et al., 2020; Uski et al., 2018). Children with brain injury are often accompanied by fluctuations in intracranial pressure (ICP) (Bennett et al., 2017). Those patients with severe brain injuries are prone to complications such as cerebral hernia, epilepsy and even death with regard to the disturbed intracranial pressure (Delaplain et al., 2020; Svedung Wettervik et al., 2020). Therefore, for children with severe brain injury, maintaining the stability of ICP is of great importance for the prognosis of patients.

Mechanical ventilation is an important way of life support for children with severe brain injury, and the airway management during mechanical ventilation plays a key role. Intratracheal suction is an important nursing operation for the management of mechanical ventilation in children (American Association for Respiratory Care, 2010). Currently, there are two kinds of methods for sputum suctions in patients with mechanical ventilation, namely open endotracheal suction and closed endotracheal suction (Afshari et al., 2014). The open sputum suction is a traditional method used in clinical practice. It has the advantages of relatively simple operation, less time‐consuming and effective, but it also has the disadvantages of aerosol exposure and interruption of mechanical ventilation (Faradita Aryani & Tanner, 2018). Different from the open endotracheal suction, the closed endotracheal suction is a kind of method developed in the last decades. It can perform sputum suction operation while ensuring the operation of mechanical ventilation, avoiding the detachment of the breathing circuit (Kuriyama et al., 2015; Letchford & Bench, 2018). To some extent, it ensures the tightness of the airway tubing, which is beneficial to maintain the oxygenation of patients, and it can reduce the risk of nursing staff being exposed to the aerosol during the suction process (Hamishekar et al., 2014). Many scholars (Copnell et al., 2007; Faraji et al., 2015; Mohammadpour et al., 2015) have evaluated the effects and safety of open suction and closed suction, but their results are inconsistent.

It is worth noting that the current research on the role of open and closed sputum suction and ICP is mostly limited to the population of adults or newborns (age < 28 days), but very few in the population of children with age < 18 years. How does sputum suction affect ICP in children with severe brain injury and mechanical ventilation? Is there any difference in the effect and safety of open and closed endotracheal suction in children with severe brain injury? These issues need to be further evaluated. Therefore, it is necessary to compare the effects and safety of open and closed endotracheal suction in children with severe brain injury, thereby providing evidence to support the airway management of children with mechanical ventilation.

## METHODS

2

### Study design

2.1

This study is designed as a single‐blinding, single‐centre randomized controlled trial (RCT), and the flow chart of study design is presented in Figure 1. We will perform blinding to the included patients, but we do not apply the blinding to the interventionists and the outcome observers.

**Figure 1 nop2656-fig-0001:**
[figure not shown]
The flow chart of study design

### Ethical considerations

2.2

This present study has been approved by the ethics committee of our present hospital (202001008–1). Any other significant potential risks and advantages will be informed to the parents and healthcare providers. And written informed consents will be obtained from all the included children or their relatives.

### Trial status

2.3

This present RCT has been registered in China Clinical Trial Registry (http://www.chictr.org.cn, ChiCTR2000030963). We have registered it on 20 March 2020. We are intended to recruit the participants on 1 September 2020, and recruitment will be completed approximately on 31 August 2022.

### Participants

2.4

The children with severe brain injury admitted to the surgical ICU (SICU) in our hospital from 1 September 2020 to 31 August 2022 will be considered for inclusion.

The inclusion criteria are as follows: (a) the age of children should be >28 days and <18 years; (b) the diagnosis of severe brain injury should comply with the relevant guidelines (Carney et al., 2017; Gao, 2017); (c) the children will undergo mechanical ventilation, and all the participants will be under the 24‐hr cerebral protection; (d) the children do not have other severe organ dysfunction, such as congenital heart disease; and (e) the guardian or relatives will be informed and agree to participate in this present study.

The exclusion criteria are as follows: (a) children with pneumothorax, atelectasis or other serious congenital diseases or respiratory infections; and (b) children or the guardians will not consent to participate in this present study and sign the informed consent.

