### Randomization and allocations

2.6

With reference to related reports, we are intended to use the method of random number table (Brocklehurst & Hoare, 2017) to randomly divide the included candidates into open endotracheal suctioning group and closed endotracheal suctioning group. We have aimed to blinding staff and patient intervention selection at the point of randomization, but once the intervention occurs then nurses can no longer be blinded. And the nurse will conduct the open and closed endotracheal suction accordingly.

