### Outcome assessment

2.9

The outcomes collected and analysed in this present study are as follows: (a) the ICP (mmHg) level before suctioning, at the end of suctioning, and at 5 and 10 min after suctioning; (b) the pulse oxygen saturation (SpO_2_,%) and heart rate (times/min) before suctioning, at the end of suctioning, and at 5 and 10 min after suctioning; (c) the estimated sputum volume (ml) for each suction; (d) the incidence of ventilator‐associated pneumonia(VAP): the diagnosis and treatment of VAP will be in comply with related guidelines (Ardehali et al., 2020; Liapikou et al., 2019; Shi et al., 2019); (e) the duration of mechanical ventilation (days); and (6) the length of ICU stay (days).

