### Statistical analysis

2.10

SPSS 23.0 software will be used for data analysis in the present study. The enumeration data will be expressed with mean ± standard deviation (*SD*), and the categorical variable data will be expressed with percentages (%). Test for normality will determine whether to use parametric test (independent *t* test/paired *t* test) or (Mann–Whitney test/ Wilcoxon's test). In this present study, *p* < .05 will be considered statistically significant.

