## RESULTS

3

Our study is planned to commence on 1 September 2020 and is expected to run until 31 August 2022, with a total duration of 24 months. We will use the intention‐to‐treat analysis to retain the randomized information as much as possible, and we will compare and adjust the characteristics to minimize the homogeneity of participants. We have conducted a pilot study with four patients to check the feasibility of the study, and it is feasible in our department. And based on the results of pilot study, we expected that the closed suctions may have more advantages in stabilizing the ICP level, and it may have the equal effects in the suctioned sputum volume and preventing the VAP. The results are expected to be shared in August 2022.

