ICP monitoring plays an important role in the treatment and prognosis of patients with brain injury. Several previous studies (Argent, 2019; Chen et al., 2019; Miles et al., 2020) have shown that there is a significant correlation between the changes in ICP and cerebral blood flow perfusion with various treatment and nursing procedures. The nursing operation of suction can lead to transient increase in ICP, but its long‐term effects remain unclear. Giancarlo et al (Galbiati & Paola, 2015) have systematically analysed 14 related studies and have pointed out that although the risk of ICP increasing above 20mm Hg during open suction is higher, it is still unclear which suction approach is more conducive to the maintenance of ICP and brain blood perfusion balance. Therefore, further research is needed to determine the best suction technique for nursing practice.

Several limitations must be considered in this present study. Firstly, even though we have organized a research team to collect the data, we cannot ensure all the normal nursing staff will follow the procedures as we designated, we cannot ensure data are collected on every suction episode, especially for those patient requires emergency suctioning, and the data may not be collected timely. We will conduct several trainings on the details of our procedure to ensure the accuracy of collected data. Secondly, sample size is not large in this present study, and there may be some differences in the suction pressure among different populations, and future studies with larger sample size and multi‐centre are needed.

To the best of our knowledge, there are very few studies focused on the role of open and closed endotracheal suctions and potential effects on the ICP in the children population. In this present study, we have aimed to assess the potential effects of open and closed endotracheal suction on ICP in the population of children, to provide credible evidence to the nursing care of airway. The results of this study are expected to provide basis for the suction practice of airway management in children.

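### Sputum volume is compared in raw mL, without a covariate, in children aged 29 days to under 18 years, which costs precision where the plan expects no difference

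*Protocol article*

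**What the plan says.** Section 2.4 (Participants) sets the age limits: "the age of children should be >28 days and <18 years". Section 2.6 assigns arms by a random number table ("we are intended to use the method of random number table") and names no stratification factor.

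Section 2.9 lists as outcome (c) "the estimated sputum volume (ml) for each suction". The unit is absolute mL, not related to age or weight.

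Section 2.10 says "Test for normality will determine whether to use parametric test" or its rank-based counterpart. The tests named are the independent and paired t tests, Mann-Whitney and Wilcoxon. No regression or covariance model appears.

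The Results section adds that "we will compare and adjust the characteristics to minimize the homogeneity of participants". It names no covariate, model or outcome. The aim as worded is reversed, since adjustment would be meant to deal with differences between participants. The same section says of closed suction that "it may have the equal effects in the suctioned sputum volume and preventing the VAP".

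**The concern.** Body size differs greatly between a one-month-old and a seventeen-year-old, and the volume obtained at one suction plausibly rises with it. If so, part of the spread in mL has nothing to do with the suction method. A test that takes no covariate leaves all of that spread in the standard error.

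This matters more than usual because the expected sputum result is no difference. Noise works in favour of that expectation: a wide interval and a p value above 0.05 can be read as showing that closed suction clears as much sputum as open suction. The Discussion links poor sputum removal to oxygenation and to the risk of ventilator-associated pneumonia, so the sputum comparison carries clinical weight.

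**Working it through.** **Inputs from the protocol article.** 86 children per arm, 172 in total, and significance at p < 0.05 (taken as two-sided); β = 0.2, so 80% power.

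**Inputs that are assumed.** The documents give no SD of sputum volume, no age distribution, and no share of variance explained by age or size (R²). I take R² from 0.1 to 0.8, with 0.25 to 0.5 as the central range, and one sputum value per child.

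**The plan's own figures.** None is given for sputum. Section 2.5 sizes the trial on fluctuation rates of 54.6% and 20.9%. Its last steps reproduce: 78 × 1.10 = 85.8, so 86, and 2 × 86 = 172. The 78 does not: the printed formula with λ = 8.84 gives 8.84 / (2 × 0.3567²) = 34.7. That is a separate matter. Here 86 per arm is simply the planned size.

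**Step 1: detectable difference after adjustment.** In residual SDs, (1.960 + 0.842) × √(2/86) = 2.802 × 0.1525 = 0.427.

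**Step 2: the same difference on raw mL.** The total SD is the residual SD divided by √(1 − R²), so power = Φ(2.802 × √(1 − R²) − 1.960). The equivalent number per arm is 86 × (1 − R²). The cut in standard error from adjusting is 1 − √(1 − R²).

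| R² (assumed) | Power on raw mL | Equivalent n per arm | Cut in standard error from adjusting |
|---|---|---|---|
| 0.10 | 76% | 77 | 5% |
| 0.25 | 68% | 65 | 13% |
| 0.50 | 51% | 43 | 29% |
| 0.80 | 24% | 17 | 55% |

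For R² = 0.25: 2.802 × 0.866 − 1.960 = 0.466, and Φ(0.466) = 0.68. For R² = 0.50: 2.802 × 0.707 − 1.960 = 0.021, and Φ(0.021) = 0.51.

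**Step 3: is that R² range plausible?** Assume ages uniform over the eligible range, weights of about 4 to 62 kg, and a residual coefficient of variation of 0.5 to 1.0. If volume is proportional to weight, weight explains 34% to 62% of the variance of log volume, and the standard error falls by 19% to 38%. If volume follows the square root of weight, the fall is 6% to 16%. The gain therefore runs from small to substantial, depending on scaling that the documents do not describe.

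**Step 4: is there bias?** The chance standardised age difference between arms has standard error √(2/86) = 0.1525, so 95% of trials lie within ±0.30. At that limit the mean sputum shift is 0.299 × √R²: 0.09, 0.15, 0.21 and 0.27 total SDs for R² of 0.1, 0.25, 0.5 and 0.8. All are below the 0.43 SD that the trial could detect. In 20,000 simulated trials without a treatment effect, the unadjusted t test had type I error of 4.9%, 4.9% and 5.1% at R² of 0.25, 0.5 and 0.8. In the roughly 10% of trials whose standardised age difference exceeded 0.25, it was 15%, 23% and 40%. Adjustment also deals with that conditional error.

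**Step 5: would mL/kg do instead?** Only under proportional scaling. If volume follows the square root of weight, then log(mL/kg) = −0.5 × log(weight) + error, whereas log(mL) = +0.5 × log(weight) + error. The two have the same variance, so dividing by weight gains nothing.

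**The case against.** The strongest reply is that this is a condensed article. The Results section does promise adjustment, and the choice of covariates is commonly left to an analysis plan, which is not shown. That has force: the missing covariate names alone would not be a finding. What remains is a mismatch in what the article does state. Section 2.10 fixes tests that cannot adjust for anything, while the Results section says that adjustment will be made.

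It is also fair that sputum volume is not the outcome on which the trial was sized, that the title and sample size centre on ICP, and that the size of the gain rests wholly on assumptions. At the low end it is slight.

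A reader might infer something stronger: that a plain random number table over this age range lets age imbalance swamp the sputum comparison. The documents do not support that. Randomisation leaves the comparison unbiased, chance imbalance is already reflected in the standard error, and the shift at the 95% limit stays below the detectable difference. That allocation is unstratified is itself inferred from silence in section 2.6.

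Nor does the Discussion concede the point. Its remark that "there may be some differences in the suction pressure among different populations" is about suction pressure, not about secretion volume by age.

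The point should not be stretched to ICP and heart rate either. Both have a pre-suction value (section 2.9), and comparing changes from it removes stable age differences in level.

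**Conclusion.** The point holds as a loss of precision on one outcome, not as bias. At 86 per arm, and if age or size explains 25% to 50% of the variance in sputum volume, using raw mL without a covariate lowers power from 80% to about 68% to 51%. That equals analysing 65 to 43 children per arm instead of 86. If the true share is nearer 10%, the loss is small (76%). These figures rest on an assumed R², a normal approximation and one value per child.

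The change is worth making because it is cheap and because imprecision here leans towards the result that the plan expects. Adjustment would not turn a non-significant p value into proof of equality. It narrows the interval from which any such claim would be judged.

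**What to change.** In section 2.10, state that sputum volume will be compared between arms by a regression on (log-transformed) volume, with arm and either age or body weight as a prespecified covariate. State how zero-yield suctions will be handled, since they have no logarithm. Report raw mL by arm as description only, and do not rely on mL/kg as the substitute, because it assumes proportional scaling. Align the adjustment sentence in the Results section with this: name the covariate and the outcome, and correct the reversed wording of its aim.

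The cost is one variable that the chart should already hold and one degree of freedom. No extra patients are needed, and the change can be made before analysis even if allocation has begun. Age-stratified allocation is optional and not part of the required change; in an unblinded single-centre trial, blocking within strata makes assignments somewhat more predictable.

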### Sample size calculation

2.5

We calculate the sample size with the following formula for the rate comparison of two groups (Sakpal, 2010):$$n=\frac{\lambda }{2{\left(\arcsin\sqrt{P_{\max}}‐\arcsin\sqrt{P_{\min}}\right)}^{2}}$$We assume α = 0.05, β = 0.2 and ν = 3–1 = 2, then λ = 8.84, and we set *P*
_max_ and *P*
_min_ as the maximum and minimum fluctuation rates of during sputum suction in our pre‐trials (54.6% and 20.9%, respectively), then we come to the result of *n* ≈ 78. Furthermore, considering that the attrition rate of about 10% of the study participants, the number of patients included in each group should be at least 86. Therefore, a total of 172 patients are intended to be included.

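### The sample size rests on a comparison of two fluctuation rates that are not defined as an outcome and have no named test, so the stated 80% power does not describe the planned ICP comparison

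*Protocol article*

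**What the plan says.** The protocol article, section 2.5, uses a "formula for the rate comparison of two groups". Its inputs are α = 0.05, β = 0.2, ν = 2, λ = 8.84 and two rates ("54.6% and 20.9%, respectively"), described as "the maximum and minimum fluctuation rates of during sputum suction in our" pre-trials. The result is n ≈ 78 per group. After allowing for "the attrition rate of about 10% of the study participants", it states that "the number of patients included in each group should be at least 86", 172 in all.

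Section 2.9 opens its outcome list with "a) the ICP (mmHg) level before suctioning, at the end of suctioning, and at 5 and 10 min after suctioning". The other items are SpO2 and heart rate at the same times, sputum volume, VAP incidence, ventilation days and ICU days. No fluctuation rate, threshold or event appears, and no outcome is named as primary.

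Section 2.10 says "Test for normality will determine whether to use parametric test" (independent or paired t test) or a rank test (Mann–Whitney or Wilcoxon). Categorical data are to be summarised as percentages.

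**The concern.** A power statement has meaning only for a particular endpoint analysed by a particular test. Here the three sections that should agree do not. Section 2.5 powers a comparison of two rates, section 2.9 defines ICP as a continuous level, and section 2.10 tests continuous or ranked values. The α and β of section 2.5 are thus attached to a comparison that the rest of the document does not set out.

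Two things are at stake. The reader is not told what ICP difference the trial can detect, although ICP is the outcome in its title. And the gap leaves room to choose, after the data are seen, between mmHg levels and a fluctuation measure defined at that point. That matters more because sections 2.1 and 2.7 leave the outcome observers unblinded.

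**Working it through.** **1. The three sections side by side.**

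| Section | Quantity | Type | Method |
|---|---|---|---|
| 2.5 | Fluctuation rate, variable not named | Treated as a proportion | Arcsine formula for two rates |
| 2.9 | ICP in mmHg at four times | Continuous | None stated here |
| 2.10 | Continuous or ranked data | Continuous or ordinal | t, Mann–Whitney or Wilcoxon |

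The quantity in the first row does not recur in the other two.

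**2. The plan's own figure.** The formula in section 2.5 is n = λ / [2(arcsin√Pmax − arcsin√Pmin)²], in radians.

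- arcsin√0.546 = 0.8315 and arcsin√0.209 = 0.4748; the difference is 0.3567 and its square 0.1272.
- n = 8.84 / (2 × 0.1272) = 34.7, so 35 per group. The stated 78 is not reproduced.
- Taking λ as 9.63, the value for ν = 2 at 80% power, gives 37.9, so 38. Taking 7.85, the value for ν = 1, gives 30.9, so 31.
- Leaving out the factor 2 gives 69.5 (λ = 8.84) or 75.7 (λ = 9.63).
- The usual two-sided two-proportion formula gives 32, or 37 with continuity correction.
- To obtain 78, λ would have to be 78 × 2 × 0.1272 = 19.8.

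**3. From 78 to 172.** 78 × 1.1 = 85.8, so 86 per group, and 2 × 86 = 172. With 10% loss, 86 × 0.9 = 77.4, so about 77 to 78 evaluable per arm. (Dividing 78 by 0.9 gives 87; the difference is trivial.)

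**4. Power for the stated rates at 78 per group.** By the arcsine normal approximation, 2 × 0.3567 × √(78/2) = 4.455, and Φ(4.455 − 1.960) = 0.994. That is about 99%, not 80%.

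**5. What the planned ICP comparison can detect.** For a two-sided 5% t test with 80% power, the detectable standardised difference is close to (1.960 + 0.842) × √(2/n). At n = 78 this is 0.449; the exact t calculation gives:

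| Evaluable per arm | Detectable difference (SD) |
|---|---|
| 77 | 0.454 |
| 78 | 0.451 |
| 86 (no loss) | 0.430 |

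The document gives neither an ICP difference worth detecting nor an SD, so power can only be shown over assumed values. At 78 per arm it is about 24% for 0.2 SD, 46% to 47% for 0.3, 70% for 0.4 and 87% to 88% for 0.5, depending on whether the t or the normal calculation is used. These figures assume one ICP value per child.

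**The case against.** The best defence is that a published article condenses the protocol, that section 2.10 is one short paragraph, and that a fuller analysis plan may define a fluctuation event and its test. ICP is recorded before suction, at its end, and 5 and 10 minutes later, so such a measure could be derived from planned data. This defence limits how far the point goes: it would be wrong to say that the endpoint will not be measured. It does not remove the conflict, because the article itself states a sizing quantity, an outcome list and a set of tests that do not match.

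A second objection is that section 2.5 never mentions ICP or events. The sentence lacks its noun, and maximum and minimum rates could mean the largest and smallest percentage changes. That is fair, and ICP is an inference from the title and aim. On that reading, though, a formula for proportions has been applied to a continuous change, and the stated power still does not carry over to a test of mmHg levels.

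Some stronger readings are tempting but not supported:

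- That the two rates cannot come from the pilot described in section 3 ("We have conducted a pilot study with four patients to check the feasibility of the study") and so must count suctions, not children. This needs two premises that the document does not give: that the pre-trials are that pilot, and that the rates are proportions of events.
- That a null ICP result could not be interpreted. The confidence interval for the difference would inform it, whatever the planning basis.
- That the missing test for VAP is an error. For one listed outcome among several, that is detail an article commonly leaves to a fuller document.

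**Conclusion.** The point holds as an internal conflict that should be corrected. The stated 80% power belongs to a comparison of two rates that section 2.9 does not define and section 2.10 does not test. For the ICP comparison that the document does plan, the enrolled number gives 80% power for about 0.45 SD. This assumes 77 to 78 evaluable children per arm, one value per child and a two-sided 5% t test.

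A reader might infer that the trial is too small. The documents do not show that: with no ICP difference or SD stated, 0.45 SD cannot be judged adequate or inadequate. Nor can it be compared with 54.6% against 20.9%, which lies on another scale. If the rates really are event proportions per child, 78 per group is more than the stated formula requires.

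**What to change.** Make sections 2.5, 2.9 and 2.10 describe the same endpoint, by one of two routes.

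(a) Size on the ICP level. Name the between-arm difference in ICP (mmHg) at the end of suction as the endpoint for sizing. Because suction is repeated as needed, prespecify which value or summary represents each child. Replace the power statement with wording such as: 172 children randomised, with about 77 to 78 evaluable per arm, give 80% power to detect a difference of about 0.45 SD with a two-sided 5% t test. Give the mmHg equivalent (0.45 × SD) over a stated range of assumed SDs, and say whether a difference of that size is worth detecting. Do not take the SD from the four-patient pilot, which is too small to estimate it usefully.

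(b) Keep the fluctuation rate. Supply the missing variable, define the event per child in section 2.9 and name a two-proportion test in section 2.10, reported as a risk difference with a 95% confidence interval. Say which rate is expected in which arm. Then correct section 2.5: the stated formula and inputs give about 35 per group, and 78 per group gives about 99% power for those rates. Adding a definition and a test alone would leave a wrong n in place. If the rate is a percentage change, route (b) does not apply and the formula must be replaced by one for a continuous outcome.

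Either route is a change of wording in three sections. Neither needs more children or additional measurements. The cost is that the sample-size justification must be restated openly.

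### The stated 78 per group does not follow from the printed sample-size formula, which gives 35 with the plan's own inputs and 31 with two-group inputs

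*Protocol article*

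**What the plan says.** Section 2.5 (Sample size calculation) presents its method as a "formula for the rate comparison of two groups" and prints n = λ / [2(arcsin√Pmax − arcsin√Pmin)²]. The inputs are given as "We assume α = 0.05, β = 0.2 and ν = 3–1 = 2, then λ = 8.84". Pmax and Pmin are the largest and smallest fluctuation rates during suction in the authors' pre-trials, and the text runs from these rates straight to the answer: "54.6% and 20.9%, respectively), then we come to the result of" n ≈ 78. After an allowance for about 10% attrition, "the number of patients included in each group should be at least 86", which gives 172 in total.

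Section 2.6 (Randomization and allocations) says the trial will "randomly divide the included candidates into open endotracheal suctioning group and closed endotracheal suctioning group", so there are two arms.

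**The concern.** The formula, every input and the result are all legible in one paragraph, so the result should be reproducible by hand, and it is not. The degrees of freedom are those of a three-group comparison, although the same section and section 2.6 both describe two groups.

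This paragraph is the article's only justification for enrolling 172 children with severe brain injury. As printed, it does not tell a reader what difference the trial was sized to detect, or with what probability. Anyone who takes β = 0.2 at face value for 54.6% versus 20.9% would misjudge the design.

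**Working it through.** **Inputs, all from section 2.5 unless noted.** α = 0.05; β = 0.2; ν = 2; λ = 8.84; Pmax = 0.546; Pmin = 0.209; stated n = 78 per group before attrition, 86 after, 172 in total. Number of arms: two (section 2.6).

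**Step 1: the plan's own figure.**
- arcsin√0.546 − arcsin√0.209 = 0.8315 − 0.4748 = 0.3567 rad; squared, 0.1272.
- n = 8.84 / (2 × 0.1272) = 34.7, so 35 per group.
- The stated 78 is 78 / 34.7 = 2.2 times this. To obtain 78 from the printed formula and rates, λ would have to be 78 × 2 × 0.1272 = 19.8.

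**Step 2: the inputs.** λ is the noncentrality at which a chi-square test with ν degrees of freedom at α = 0.05 has power 0.80. For ν = 1 it equals (1.960 + 0.842)² = 7.85. For ν = 2 it is 9.63, solved numerically.

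| ν | λ | n from the printed formula | per group |
|---|---|---|---|
| 2, as printed | 8.84, as printed | 34.7 | 35 |
| 1 (two groups) | 7.85 | 30.9 | 31 |
| 2 (three groups) | 9.63 | 37.9 | 38 |

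The printed λ = 8.84 corresponds to power of 84.5% at ν = 1 or 76.3% at ν = 2, and neither is 80%. As a cross-check, the usual two-sided two-proportion formula at 80% power gives 32 per group, or 37 with continuity correction.

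**Step 3: is there a reading that gives 78?** Dropping the factor 2 gives 69.5 with the printed λ, or 75.7 with λ = 9.63. Neither is 78, and both alter the printed formula. Dropping both the factor 2 and the arcsine transform gives 8.84 / (0.546 − 0.209)² = 77.8, which matches. This may be how 78 arose, but nothing in the text shows it.

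**Step 4: what the planned size delivers, if the two rates are per-patient proportions in the two arms.**
- With 10% lost, 86 × 0.9 = 77.4, so about 77 evaluable per group.
- Power for 54.6% versus 20.9%: Φ(2 × 0.3567 × √(77/2) − 1.960) = Φ(2.47), about 99%. At 78 per group it is 99.4%.
- Rate detectable with 80% power against 54.6%: sin²(0.8315 − √(7.85 / 154)) = sin²(0.6057), about 32%.

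**The case against.** The strongest case on the other side concedes the mismatch and attacks what might be built on it. Four inferences are tempting.

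- **That the trial has 99% power.** The documents do not support this as an unconditional statement. Section 2.5 gives no arm, event or unit for the fluctuation rates. The only pilot described (section 3, Results) had four patients. If that is the pre-trial meant, a proportion of patients could only be 0, 25, 50, 75 or 100%, so neither rate could be one. No fluctuation rate is listed among the outcomes in section 2.9, and the tests named in section 2.10 are t, Mann–Whitney and Wilcoxon tests. This objection stands: the power figures are conditional.
- **That a claim of achieved 80% power is false.** The article gives "α = 0.05, β = 0.2" as design inputs and makes no separate claim of achieved power. What fails is n, given those inputs.
- **That the attrition step is a further error.** 78 × 1.1 = 85.8, rounded to 86, is a common convention, and the allowance is only about 10%. Dividing by 0.9 gives 87, one more child per group. This is not counted as an error.
- **That the origin of 78 is known.** The match to 77.8 is numerical only. Another reading is that 78 is a two-group total already inflated for attrition: 35 / 0.9 = 38.9, so 39, and 2 × 39 = 78.

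The errors in ν and λ move the formula's answer only between 31 and 38, so neither of them produces 78. None of these objections restores the stated figure.

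**Conclusion.** The paragraph is wrong as written. The printed formula with the printed inputs gives 35 per group, against 78 stated. With the degrees of freedom that fit two arms and the matching λ, it gives 31. The stated size is therefore 2.2 to 2.5 times what the stated target requires (78/35 and 78/31), and β = 0.2 does not describe it. This much rests on section 2.5 alone, together with the two arms confirmed in section 2.6.

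The direction matters. A reader might infer that the trial is underpowered, and on the stated inputs the opposite holds. A reader might also infer that enrolment should be cut to about 31 per group. That does not follow either, because the rates are not tied to any listed outcome, so the target itself is undefined. The figures of about 99% power and a detectable rate of about 32% assume per-patient proportions in the two arms, two-sided α = 0.05 and about 77 evaluable per group.

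**What to change.** In section 2.5:

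1. Replace ν = 3 − 1 = 2 with ν = 2 − 1 = 1, and λ = 8.84 with 7.85.
2. State that the formula then gives 31 per group for 54.6% versus 20.9%.
3. Say which outcome the two rates measure, whether the unit is the patient or the suction episode, and which arm each rate belongs to.
4. Keep 172 as the planned total and restate what it delivers. If item 3 confirms per-patient proportions in the two arms, the text can say that about 77 evaluable per group gives about 99% power for 54.6% versus 20.9%, or 80% power for 54.6% versus about 32%. If item 3 shows anything else, those figures should not be printed, and the size should be justified on the outcome actually intended.

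The attrition step needs no change. The cost is a corrected paragraph, with no extra patients and no change to the design.
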